#### Personalised tele-based coaching

The personalised tele-based coaching is provided by the company IVPNetworks (www.ivpnetworks.de) and focuses on general mental health problems. The coaches are psychologists with trainings either in cognitive behavioural therapy, systemic therapy, psychodynamic psychology, hypnotherapy or other therapeutic trainings. Licensed psychotherapists are responsible for supervision. The coaches support participants in recognising and understanding conflict patterns in order to effectively cope with issues by activating their own resources. This is pursued by approaching the participant’s personal situation and stressors (e.g., financial burden, family problems, work-related stress).

Participants are registered with their contact information in the IVPNetworks management and documentation platform (IVPnet 2.0). A case manager at IVPNetworks assigns the participant to a coach. The coaching is personalised in terms of amount, frequency and duration of the sessions, depending on the individual participant’s needs. Personalised coaching means that there are no standardised manuals or fixed procedures for the coaching. Different therapeutic methods are used depending on the therapeutic background of the coach (which will be monitored in the study). If indicated, participants are supported in finding on-site social and health care services to complement the tele-based coaching (e.g., socioeconomic consultants, agricultural family counselling). Alternatively, on-site coaching can be arranged if a participant no longer prefers tele-based coaching. Common content and duration of the personalised tele-based coaching at IVPNetworks are illustrated in Fig. 3.

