#### Quantitative analysis

The evaluation of the implementation follows the RE-AIM dimensions as described above. Descriptive analyses (frequencies, means and percentages) will be performed to assess outcomes across all RE-AIM dimensions. We will evaluate the implementation success of the internet- and tele-based interventions separately.

To assess the representativeness of the participants compared to the target group, t-tests or non-parametric tests will be used. To assess intervention effectiveness, we analyse for different groups of participants (e.g. participants who have started treatment or completed treatment) by using independent sample t-test and chi-squared analyses. We will use t-tests or non-parametric tests to analyse differences between pre-, post- and follow-up-measurements. In order to counteract the issue of multiple comparisons, Bonferroni correction is used. The statistical significance level is set to *p* < .05. Within-group effect sizes and 95% CIs will be reported at all measurement points. Implementation effectiveness is assessed by comparing uptake rates, the degree of normalisation among staff-participants and efficiency outcomes (costs of implementation effort in relation to uptake and degree of normalisation) at different time points.^4^

Furthermore, linear regression models are used to investigate differences between the interventions (guided IMIs, personalised tele-based coaching and on-site group workshops) regarding reach outcomes (referral and uptake rates) with intervention type as independent variable. By using further linear regression models we compare socio-demographic and clinical outcomes as dependent variables between the participants of the different prevention services (independent variable). Based on multiple linear regression models we analyse the influence of factors at staff level (credibility of the internet- and tele-based interventions, degree of normalisation, leadership support, organisational readiness to change and determinants of behavioural change) as independent variables on the number of referrals by field workers, in-house staff and call centre agents (dependent variables). Additionally, the implementation outcomes will be compared between the federal states and rollout areas at different phases of implementation.

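### Tele-coaching outcomes are analysed as if participants were independent, so their 95% CIs will be too narrow if outcomes correlate within coach

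*Protocol article*

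**What the plan says.** The Quantitative analysis section of the protocol article names its methods for participant outcomes. For change over time: "We will use t-tests or non-parametric tests to analyse differences between pre-, post- and follow-up-measurements". For groups such as starters and completers, effectiveness is analysed "by using independent sample t-test and chi-squared analyses". For the services: "By using further linear regression models we compare socio-demographic and clinical outcomes as dependent variables between the participants of the different prevention services". On output it promises: "Within-group effect sizes and 95% CIs will be reported at all measurement points". On testing: "The statistical significance level is set to *p* < .05", with a Bonferroni correction. No random effect and no cluster-robust standard error is named for any of these.

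The section on personalised tele-based coaching says that a case manager at the provider assigns each participant to a coach, that "there are no standardised manuals or fixed procedures for the coaching", and that "Different therapeutic methods are used depending on the therapeutic background of the coach". It adds that the coach's background will be monitored, and the section on intervention characteristics lists it among the usage data. No stated model uses it.

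**The concern.** A t-test or an ordinary linear regression takes each participant as a separate piece of information. In tele-coaching, participants are nested in coaches, and the article itself says that what they receive varies with the coach. That is a document-based reason to expect the outcomes of participants who share a coach to be more alike than those of participants who do not. If they are, the standard error computed from participants alone is too small.

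The promised within-group intervals for tele-coaching, and the clinical contrasts between tele-coaching and other services, would then look more certain than they are. A Bonferroni correction does not help, because it adjusts the threshold and leaves the standard error as it is.

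**Working it through.** **Nothing to reproduce.** The article gives no power, effect size, SD, ICC or number of coaches. The 100 participants per intervention are called desirable, without a calculation (section on Group 1, insured persons).

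**Inputs**
- N = 100 in tele-coaching: from the article.
- Nominal 95% interval, z = 1.96: from the article; two-sided is assumed because sidedness is not stated.
- Number of coaches (5 to 50, equal caseloads): assumption.
- ICC within coach (0 to 0.10): assumption. For pre-post tests this is the ICC of the change score, not of the symptom level.

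**Formulas**, with m = N / number of coaches
- Design effect: DE = 1 + (m − 1) × ICC
- Required width relative to the naive interval: √DE
- Actual coverage of the naive interval: 2Φ(1.96/√DE) − 1
- Effective sample size: N/DE

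**Within tele-coaching, ICC 0.05**

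| Coaches | m | DE | Width ratio | Coverage | Effective N |
|---|---|---|---|---|---|
| 50 | 2 | 1 + 1 × 0.05 = 1.05 | 1.02 | 94.4% | 95 |
| 20 | 5 | 1 + 4 × 0.05 = 1.20 | 1.10 | 92.6% | 83 |
| 10 | 10 | 1 + 9 × 0.05 = 1.45 | 1.20 | 89.6% | 69 |
| 5 | 20 | 1 + 19 × 0.05 = 1.95 | 1.40 | 84.0% | 51 |

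A simulation of the one-sample t-test on change scores (40,000 runs per setting) gave coverage of 92.7%, 89.8% and 84.0% for 20, 10 and 5 coaches, which agrees with the formula.

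The naive half-width at N = 100 is 1.96/√100 = 0.196 SD of change. At ICC 0.05 it should be 0.215, 0.236 and 0.274 SD with 20, 10 and 5 coaches.

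**Sensitivity to the assumptions**
- ICC 0, any number of coaches: ratio 1.00, coverage 95.0%.
- ICC 0.01, 10 coaches: ratio 1.04, coverage 94.0%.
- ICC 0.10, 50 coaches: ratio 1.05, coverage 93.8%.
- ICC 0.10, 5 coaches: DE = 1 + 19 × 0.10 = 2.90, ratio 1.70, coverage 75.0%.

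**Internet trainings versus tele-coaching**, 100 per group, 10 participants per coach. With clustering in tele-coaching only (ICC 0.05), the variance ratio is (1 + 1.45)/2 = 1.225. The width ratio is √1.225 = 1.11 and coverage is 92.3%. With an ICC of 0.01 in tele-coaching only, the ratio is 1.02 and coverage 94.5%.

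These figures are for within-group change and for contrasts between services. They do not apply to tests of starters against completers inside tele-coaching, where both groups can share coaches and coach effects partly cancel.

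**The case against.** The strongest reply is that the article shows that methods differ by coach, not that outcomes do. Coaching is also tailored to the individual, which is variation between participants rather than between coaches. With no ICC and no coach numbers, the effect could be nil. This stands: a reader might infer that the reported intervals are certainly too narrow, and the document supports only the conditional statement.

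A second reply concerns scope. A reader might extend the point to all participants. The dependence on the coach is stated for tele-coaching only. The internet trainings are structured online modules with e-coach feedback, and nothing says that their content follows the coach. This stands too.

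A reader might also extend the point to staff and regions, since "the implementation outcomes will be compared between the federal states and rollout areas". That does not follow:
- Coach-dependent treatment has no bearing on staff referrals.
- The call centre agents work in a nationwide call centre, and the publicity is aimed at insured persons.
- There are only a pilot area and rollouts A, B and C, too few for reliable cluster-robust errors at that level.
- Where region is the comparison of interest, a random intercept for region does not repair it.

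Third, random effects and the type of standard error are often left to an analysis plan, and linear regression does not exclude cluster-robust errors. A separate plan could add a coach term. But the article does not leave the tests open: it names t-tests for the change analyses and commits to the intervals.

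Fourth, if the coaches are regarded as fixed, the naive interval is not too narrow for those particular coaches. That is correct but does not fit the stated purpose: the Discussion aims at recommendations for future interventions, which calls for inference beyond the coaches who happened to take part.

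Finally, clinical effectiveness is tested in the parallel randomised trials, and implementation success here is defined by uptake, normalisation and cost. This limits the consequence. The intervals are nevertheless a promised result.

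**Conclusion.** The point holds in conditional form, for tele-coaching and for clinical comparisons of services that include it. As written, the analysis understates the standard error of tele-coaching change, and of contrasts with it, whenever the coach ICC is above zero and coaches treat several participants each.

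With the desired 100 participants and an assumed ICC of 0.05, the understatement is modest with 20 coaches and substantial with 5. The internet-versus-tele contrast is affected less, because only one side is known to be exposed. The size rests on assumed ICCs, assumed coach numbers and equal caseloads. The documents do not support calling the intervals wrong outright, nor carrying the argument to the internet trainings alone, the staff regressions or the regional comparisons. This is a cheap improvement.

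**What to change.** 1. Obtain a pseudonymised coach ID from the tele-coaching provider. The article says that the coach's background is monitored; it does not say that coach identity reaches the study data, so this should not be taken as already available.
2. For tele-coaching outcomes and for clinical contrasts between services that include tele-coaching, replace the named tests with a linear mixed model: time (T0, T1, T2) as a fixed effect, with service and service-by-time added for the contrasts; random intercepts for participant and coach; and a term that lets change vary by coach. The last term is needed because a coach intercept alone cancels out of within-person change. Use small-sample degrees of freedom.
3. Report the coach ICC and the number of coaches with the results, so that readers can see whether clustering mattered.

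No region term for the staff regressions or regional comparisons follows from this point.

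The cost is a change of analysis wording and a small data linkage step; recruitment and assessments are untouched, and R, the software already named, can fit the model. The downsides are wider intervals and, if there are few coaches, an imprecise estimate of the coach variance.

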### Enrolment

The insured individuals are advised on the preventive services by approximately 350 employed field workers and in-house staff of SVLFG during their consultations via phone or on-site. In addition, the prevention services are advertised widely through PR activities of the SVLFG (e.g. newspaper articles, radio reports, SVLFG member magazine, lectures and information events) in the federal states where the interventions have been implemented. Interested individuals receive detailed information regarding the offered prevention services and their eligibility at the SVLFG central call centre. Eligible insured persons can choose whether they prefer single (e.g. internet- or tele-based interventions) or group preventive services. The group interventions are delivered on-site and include various topics on mental health issues for this target group (e.g. dealing with stress, handing over the business to the next generation). The registration process is conducted by SVLFG.

Data collection starts with rollout A in April 2019 and is expected to be finished at the project end (April 2021).

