	- Usage of the intervention (e.g. adherence, duration and frequency of contacts)	GET.ON Institute / IVPNetworks	Reportings	Continuous
	- Credibility (Credibility Expectancy Questionnaire) and perceived (dis-)advantages	SVLFG staff- participants	Online-assessment	R0 / R1 / R2 / R3^b^
	- Costs for the intervention	SVLFG	Reportings	Every 3 months
	*Outer Setting:*			
	Acceptance, relevance, utility	Insured person GET.ON Institute / IVPNetworks	Online-assessment Interviews Reportings (e.g. adherence)	T1^a^, T1^a^ Continuous
	*Inner Setting:*			
	- Leadership support (Implementation Leadership Scale)	SVLFG staff-participants	Online-assessment	R0 / R1^b^
	- Organisational willingness to change (Organisational Readiness for Implementing Change questionnaire)	SVLFG staff-participants, implementation team	Online-assessment	R0 / R1 / R2 / R3^b^
	*Characteristics of individuals:*			
	- Degree of normalisation (NoMAD)	SVLFG staff-participants	Online-assessment	R0 / R1 / R2 / R3^b^
	- Determinants of Behavioural Change (Discriminant Content Validation of the TDF Questionnaire)	SVLFG staff-participants)	Online-assessment	R1^b^
	- Barriers and facilitating factors at the consultations	SVLFG staff-participants	Focus groups	11/2017–02/2019
	*Process:*			
	- Evaluation of the implementation process (e.g. implementation activities, barriers and facilitating factors)	Implementation team	Interview	Every 6 months
	- Dissemination activities	SVLFG	Reportings	Every 3 months
	- Usage by employees	SVLFG staff-participants	Reportings	Every 3 months
	- Implementation costs	SVLFG	Reportings	Every 3 months
**MAINTENANCE (individual + organisatonal level)**	Sustainability of interventions (effectiveness)	Insured	Online-Assessment	T2^a^
	Referrals back to SVLFG and use of further offers	GET.ON Institute / IVPNetworks / SVLFG	Reportings	Continous
	Evaluation of the current implementation and further use of the technologies	SVLFG staff-participants	Online-assessment	R3^b^
	Sustainability of implementation (referral and uptake rates)	GET.ON Institute / IVPNetworks / SVLFG	Reportings	R3^b^

Notes

^a^time of insured-assessment depends on the date of intervention start

^b^time of employee-assessment depends on the date of the rollout in the specific area

*Abbreviation*: *m* month

Assessments: T0 (pre intervention), T1 (3 months after starting the internet-based training / 6 months after starting the tele-based intervention), T2 (12 months after starting the intervention)

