#### Maintenance

In assessing the maintenance of the implemented internet- and tele-based interventions, follow-up surveys with the insured participants will be conducted 12 months after first contact for the prevention project (e.g. 12 months after first login at the GET.ON platform or registration at IVPnet) to monitor the long-term impact of preventive interventions on mental health (see effectiveness measures, 60–65). Referrals to the SVLFG call centre are reported by the external service providers to capture all processes in the implementation that contribute to sustainable development. Uptake rates of the internet- and tele-based interventions are monitored in the maintenance phase of the respective rollout region. In terms of sustainability, we also record the use of a second IMI, the maintenance phase of the IMIs (e.g. monthly contacts for a year) or the prolongation of an IVP tele-based coaching and any other health care utilisation.

Normalisation is recorded in the maintenance phase using the questionnaire NoMAD [104] at the staff-level (e.g. field workers, in-house staff, call centre agents), and will be compared to the normalisation degree during the implementation phase. Additionally, the attitudes and experiences of the staff-participants involved in the implementation process are essential for sustained implementation. Therefore, a concluding survey with the staff-participants and important multipliers at SVLFG (e.g. management board) will be conducted at the end of the project to assess their professional view on the implementation and their intention to further use the internet- and tele-based prevention services. To ensure practical relevance, the item pool for this survey will go through an iterative feedback process with the initiators of the project.

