According the intention-to-treat principle all observed data will be included. Patterns of missing data will be analysed and corrected. All analyses will be performed with R statistic software [111].

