### Trial status

Recruitment has been started in April 2019. Participants will be continuously included until the end of the study. Data collection is ongoing.

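### Change across T0, T1 and T2 is analysed only by t-tests or non-parametric tests, which, unless missing values are imputed first, drop observed data when many T2 values are certain to be missing

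*Protocol article*

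**What the plan says.** The Quantitative analysis section gives one method for change in the symptom and quality-of-life scales: "We will use t-tests or non-parametric tests to analyse differences between pre-, post- and follow-up-measurements". It does not say whether the tests are paired, which contrasts are meant, or whether a joint three-wave test is intended. No mixed or repeated-measures model is described for this comparison.

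The same section then says "According the intention-to-treat principle all observed data will be included", followed directly by "Patterns of missing data will be analysed and corrected". No correction method is given, and nothing ties it to the tests of change.

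Three other statements fix how many people can supply each wave:
- Table 1 notes (Measurements): T1 is 3 months after starting the internet-based training or 6 months after starting the tele-based one, and "T2 (12 months after starting the intervention").
- Enrolment: "Data collection starts with rollout A in April 2019 and is expected to be finished at the project end (April 2021").
- Trial status: "Participants will be continuously included until the end of the study".

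The Maintenance section uses the 12-month survey "to monitor the long-term impact of preventive interventions on mental health".

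**The concern.** Each test that fits the stated wording has a cost when waves are missing:
- A paired t-test or signed-rank test drops anyone lacking either of its two waves.
- A three-wave rank test such as Friedman's drops anyone lacking any wave.
- An unpaired test keeps more values but ignores the within-person correlation.

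Run on the data as collected, none of these makes proper use of every observed score. Someone with T0 and T1 only adds nothing to T0-T2, although the T1 score carries information about the missing T2 score.

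Two things are at stake. One is precision at 12 months, the thinnest wave and the one on which the effectiveness part of Maintenance rests. The other is bias in the reported within-group effect sizes if those who answer differ in earlier symptoms from those who do not.

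**Working it through.** **Plan's own figure.** The article calls N = 100 per intervention desirable but gives no effect size, SD, power or dropout, so that figure cannot be reproduced. The point does not depend on it.

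**Step 1: who can reach each wave.** The window is April 2019 to April 2021, 24 months. Assume uniform accrual and no dropout. The share able to reach a wave at month t is (24 − t)/24.
- T1, internet: (24 − 3)/24 = 87.5%
- T1, tele: (24 − 6)/24 = 75%
- T2: (24 − 12)/24 = 50%
- T1 possible but not T2: 87.5 − 50 = 37.5% (internet), 75 − 50 = 25% (tele)

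Uniform accrual is an assumption. Accrual that grows as regions are added would lower the T2 share; early-loaded accrual would raise it.

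**Step 2: precision when response is unrelated to symptoms.** Assumed: 100 starters; correlations 0.50 (T0-T1), 0.60 (T1-T2) and 0.45 (T0-T2); unit SD; true change −0.40 SD at both T1 and T2. The complete-pair standard error is sqrt(2(1 − 0.45)/pairs) = sqrt(1.1/pairs). The joint estimate is the likelihood estimate for monotone missingness: T1 is regressed on T0, T2 on T0 and T1, and both are evaluated at the mean T0 of all starters.

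| Response at T1, then at T2 among those | Pairs | Formula SE | Simulated pair SE | Joint SE | Variance ratio |
|---|---|---|---|---|---|
| 70%, 70% | 49 | 0.150 | 0.151 | 0.137 | (0.151/0.137)² = 1.21 |
| 60%, 60% | 36 | 0.175 | 0.177 | 0.155 | (0.177/0.155)² = 1.30 |
| 80%, 50% | 40 | 0.166 | 0.167 | 0.146 | (0.167/0.146)² = 1.31 |

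Both approaches are unbiased here.

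A second set of inputs used all correlations 0.6, the Step 1 calendar, and dropout of 20% then 15%, or 40% then 30%. It left about 45 to 70 T0-T1 pairs and 21 to 34 T0-T2 pairs per 100 entrants. The variance ratios were:
- Internet: (0.157/0.141)² = 1.24 and (0.200/0.186)² = 1.16
- Tele: (0.156/0.145)² = 1.16 and (0.198/0.182)² = 1.18

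**Step 3: bias when response falls with the previous score.** With the first set of inputs and log-odds of response falling by 0.4 to 0.7 per SD (truth −0.40 SD):
- T0-T1 pairs give −0.27 to −0.36 (10% to 33% too small: 1 − 0.36/0.40 and 1 − 0.27/0.40).
- T0-T2 pairs give −0.29 to −0.38 (5% to 28% too small).
- The joint model returns about −0.40 at both.

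With the second set and a slope of 1 per SD, pairs give −0.26 to −0.32 and the joint model −0.40. The precision gain is then mostly gone (internet: 0.160 against 0.156, and 0.196 against 0.208), so in this case the benefit is removal of bias. If improved people stop answering instead, the bias runs the other way.

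**Step 4: spurious fade or gain.** Under the first set the T0-T1 and T0-T2 pair estimates shrink nearly together and differ by about 0.01 to 0.03 SD (truth 0). Under the second set they differ by about 0.01 SD (−0.314 against −0.322; −0.262 against −0.271). The direct T1-T2 pair contrast moves more under the first set, by 0.05 to 0.13 SD.

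**The case against.** The strongest reply is that the article does not contradict itself. The sentence on missing data follows directly. If it means imputation, the same people enter every test and nothing is lost. A condensed article may leave the imputation method to a fuller document, and the phrase on including all observed data may mean only that nobody is excluded for non-adherence. This stands in part: the conflict is conditional, and the absence of a named correction is not the point on its own. What the article does state is the test, and that test cannot use the partial records unaided.

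A reader might infer that the T1 and T2 changes come from different people. The text does not support this. The subsets overlap, most people with T2 will also have T1, and a three-wave test on one common set is not excluded.

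A reader might also infer that an apparent fade or gain at 12 months could be largely an artefact of who answered. On the comparison usually read for this, T0-T1 against T0-T2, the calculation shows 0.01 to 0.03 SD, which is negligible.

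It is also fair that all correlations and dropout rates are assumed, and that the biased scenarios use the very mechanism under which the joint model is consistent. The only missingness the article makes certain is administrative. If that is unrelated to symptoms, complete pairs are unbiased and the cost is a standard error about 10% to 14% larger (square roots of 1.21 and 1.31).

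Finally, implementation success is defined by uptake, normalisation and efficiency, and parallel randomised trials address clinical effectiveness. This limits the weight of the point but does not make the stated test the better choice.

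**Conclusion.** The point holds in a conditional form. The only stated analysis of change is a set of tests that, without prior imputation, leave out observed values, and the study calendar makes many missing T2 values certain. Under uniform accrual, at most about half of entrants can reach T2.

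Under the assumed inputs, the T0-T2 variance is about 20% to 30% larger than with a joint model when response is unrelated to symptoms (16% to 24% under the second set). If response depends on earlier observed scores, both the T1 and T2 changes are biased, and the joint model removes this under missing at random. The direction depends on who stops answering.

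The documents do not support a claim of outright self-contradiction, of separate populations at T1 and T2, or of a material false fade or gain between the T0-T1 and T0-T2 changes. The matter affects a supporting outcome and is cheap to put right.

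**What to change.** For each scale and each service, make the primary analysis of change one linear mixed model for repeated measures, with time (T0, T1, T2) as a factor and unstructured covariance, using every observed value of every starter. Take the T1-T0, T2-T0 and T2-T1 contrasts, with 95% confidence intervals and effect sizes, from that one model. Keep the paired t-tests or rank tests as a sensitivity analysis.

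Multiple imputation that includes all three waves, applied before the tests, is an acceptable equivalent. In that case the plan should name it as the missing-data correction and tie it to these comparisons.

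The cost is a change of wording and a few lines in R, the software already named. No new data are needed. The limitation is reliance on missing at random: neither route cures dropout that depends on unobserved scores, and the report should say so.

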### Measurements

The used measures are summarised in Table 1, followed by a description of each RE-AIM dimension and selected outcomes. Measurements include routine data, staff reviews of intervention consultations as well as usage of the interventions by insured individuals, online-assessments, qualitative interviews and focus groups.

**Table 1 Tab1:** RE-AIM dimensions, measures and assessments

Dimension	Measure	Source	Assessment type	Time point
**REACH (individual level)**	Number and characteristics of potentially eligible insured individuals	SVLFG	Routine data	18 m
	Exclusion, referral und uptake rates; Completer rating from clinician’s judgement (Helping Alliance Questionnaire)	GET.ON Institute / IVPNetworks / SVLFG; GET.ON and IVP coaches	Reportings; Online-Assessment	Every 3 months; after participant is defined as (non-) completer
	Estimated number of people exposed to the recruitment, recruitment response rate in general as well as specific recruiting strategies	GET.ON Institute / IVPNetworks / SVLFG	Reportings	Every 3 months
	Representativeness of participants compared to eligible insured individuals and interested, but not participating insured persons	SVLFG	Routine data	18 m
**EFFECTIVENESS (individual level)**	Depressive symptoms (Patient Health Questionnaire 9), perceived stress (Perceived Stress Scale 4), generalised anxiety disorder (Generalised Anxiety Disorder 7 scale), somatisation (Somatic Symptom Scale 8), health-related quality of life (Assessment of Quality of Life 4D), subjective capacity to work (Subjective Prognostic Employment Scale)	Insured person	Online-assessment	T0-T2^a^
	Patient satisfaction (Client Satisfaction Questionnaire adapted for internet interventions), side effects (Assessment of Negative Effects of Psychotherapy)	Insured person	Online-assessment	T1^a^
**ADOPTION (organisational level)**	Number, proportion and characteristics of involved employees per organisation, characteristics of federal states and rollout areas, characteristics of insured persons and type of agricultural holding	GET.ON Institute / IVPNetworks / SVLFG	Sociodemographics of employees, routine data	R0^b^ Continuous
**IMPLEMEN-TATION (individual + organisational level)**	*Characteristics of the interventions:*			
	- Adaptations (TIDieR checklist)	GET.ON Institute / IVPNetworks	Reportings	Mid and end of the project

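### Bonferroni is valid here, but Holm's step-down procedure gives the same family-wise protection, never rejects less and usually rejects more: a free, low-severity improvement

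*Protocol article*

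**What the plan says.** The Quantitative analysis section of the Protocol article plans the outcome-by-time tests as follows: "We will use t-tests or non-parametric tests to analyse differences between pre-, post- and follow-up-measurements". It then states: "In order to counteract the issue of multiple comparisons, Bonferroni correction is used". The level follows: "The statistical significance level is set to" p < .05. The same paragraph promises within-group effect sizes with 95% confidence intervals and does not describe those intervals as simultaneous or adjusted.

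Table 1 (Measurements) lists six self-report scales under Effectiveness: "Depressive symptoms (Patient Health Questionnaire 9), perceived stress (Perceived Stress Scale 4), generalised anxiety disorder (Generalised Anxiety Disorder 7 scale"), followed by "somatisation (Somatic Symptom Scale 8), health-related quality of life (Assessment of Quality of Life 4D), subjective capacity to work (Subjective Prognostic Employment Scale"). All six are measured from T0 to T2, the last being "T2 (12 months after starting the intervention"). On the two services the section says: "We will evaluate the implementation success of the internet- and tele-based interventions separately".

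The section on Group 1 (insured persons at SVLFG) calls N = 100 per intervention desirable and expects roughly 500 to 800 participants in all. The article states neither the number of tests in the corrected family nor a power figure.

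**The concern.** Six scales at three visits make 12 tests per service if each later visit is compared with baseline, or 18 if all three pairs of visits are compared. With 18 tests, Bonferroni holds every one of them to 0.05/18, however many of the others have already been rejected. Holm relaxes the threshold as rejections accumulate and gives up nothing in family-wise error. The article names the weaker of two procedures that offer the same guarantee.

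At stake is how many real changes on these scales are declared. The validity of any declared change is not in question. The stakes are limited, because the article defines implementation success by uptake, normalisation and efficiency (Measuring implementation success), and the clinical scales belong to one RE-AIM dimension.

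**Working it through.** **Inputs from the article.** Six scales, three visits, level 0.05, N = 100 per intervention as the desirable size, 500 to 800 expected in total. An even split over two services, which is my assumption, gives 500/2 = 250 to 800/2 = 400 each.

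**Inputs assumed.** Two-sided normal tests; all three pairwise contrasts, so m = 6 × 3 = 18 per service; a change at T1 held to T2, so 12 contrasts are real and the six T1–T2 contrasts are null; correlation 0.5 between outcomes and 0.6 over time; standardised within-person change of 0.2 to 0.4.

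**Step 1: the stated method is valid.** The per-test level is 0.05/18 = 0.00278, and 18 × 0.05/18 = 0.05. For m = 12, 12 × 0.05/12 = 0.05. Family-wise error is at most 5% under any dependence. Unadjusted independent tests would give 1 − 0.95^12 = 46.0% or 1 − 0.95^18 = 60.3%, so some correction is needed.

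**Step 2: Holm's thresholds.** Order the p-values and reject the i-th smallest while p(i) ≤ 0.05/(m − i + 1), stopping at the first failure. For m = 18 the thresholds run 0.05/18 = 0.00278, 0.05/17 = 0.00294, and so on, reaching 0.05/7 = 0.00714 at the twelfth. None is below 0.05/18, so every Bonferroni rejection is kept. The first equals the Bonferroni threshold, so the chance of at least one rejection is identical.

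**Step 3: Bonferroni power in closed form.** The two-sided critical value at 0.05/18 is z = 2.991, and power per real contrast is Φ(d√n − 2.991).
- n = 100, d = 0.3: Φ(3.000 − 2.991) = 50.3%
- n = 100, d = 0.4: Φ(4.000 − 2.991) = 84.3%
- n = 250, d = 0.2: Φ(3.162 − 2.991) = 56.8%
- n = 250, d = 0.3: Φ(4.743 − 2.991) = 96.0%

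**Step 4: Holm power by simulation** under the same model, averaged over the 12 real contrasts:

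| n | change | Bonferroni | Holm |
|---|---|---|---|
| 100 | 0.3 | 50–51% | 56% |
| 100 | 0.4 | 84% | 89% |
| 250 | 0.2 | 57% | 63% |
| 250 | 0.3 | 96% | 98% |
| 400 | 0.3 | 99.9% | 100% |

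Simulated Bonferroni power in the first row falls at 50% or 51%, around the closed-form 50.3%. Holm's family-wise error was at most about 4%, and no Bonferroni rejection was lost in any run.

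**Step 5: dependence on the family.** With only the two contrasts from baseline (m = 12, correlation 0.5, n = 100, change 0.3), the gain is larger if all 12 are real (55.6% to 67.2%) and smaller if half are (55.3% to 58.7%). In both cases the chance of at least one rejection is unchanged.

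**The case against.** The strongest reply is that nothing is wrong. Bonferroni is valid and prespecified, it contradicts no other part of the article, and the article makes no power claim for it to undermine. All of that stands, so this is an improvement and not the correction of an error.

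A reader might infer more than the article supports, in four ways.
- *That Holm has strictly more power.* It is never less powerful, but for rejecting at least one hypothesis the two are equal.
- *That correlation between the scales is the reason to switch.* Holm does not use correlation either. Its advantage exists at correlation 0, and with no true effects the two are equally conservative (for m = 12, family-wise error 5.0%, 3.7% and 2.2% at correlations 0, 0.5 and 0.8).
- *That 18 tests gain more than 10 points.* Such a figure (50.4% to 62.0% at n = 100, change 0.3) gives all 18 contrasts the same standardised effect. The T0–T2 change is the sum of the T0–T1 and T1–T2 changes, so equal non-zero effects require SD(T0–T2) = SD(T0–T1) + SD(T1–T2). That holds only if the two successive changes correlate at exactly 1.
- *That about 100 participants per service are expected.* The article calls that number desirable per intervention and expects 500 to 800 overall. At 250 or more per service, the choice barely matters for a change of 0.3.

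Two practical objections remain. The article does not say which tests form the corrected family, so prescribing a narrower one could weaken the control. Bonferroni also has simple matching simultaneous intervals, which Holm lacks. Neither blocks the change: Holm can be applied to whatever family the plan would already correct, and the planned 95% intervals are not described as simultaneous.

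**Conclusion.** The point holds as a free improvement of low severity. The superiority of Holm in the sense given (same family-wise error, no rejection lost, usually some gained) is a mathematical result and rests on no assumed input. The size of the gain does rest on assumptions: effect sizes, correlations, the number of tests, how many changes are real, and how participants split between services. Under the coherent three-visit model it is about 5 points of average power at n = 100, about 6 points at n = 250 for a change of 0.2, and under 2 points at n = 250 or more for a change of 0.3. The documents do not support reading this as a flaw in error control or as a threat to the study's conclusions.

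**What to change.** In the Quantitative analysis section, name the Holm-Bonferroni correction in place of the Bonferroni correction, applied to the same family of tests that the plan would otherwise correct with Bonferroni. Keep the planned effect sizes and 95% confidence intervals, and label the intervals as not adjusted for multiplicity. Make the change before the data are analysed.

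The cost is one sentence and one built-in option in R, which the article already specifies. Family-wise error control is unchanged, no further data are needed, and no planned analysis is dropped.
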